### Usual Care

Both groups will receive usual standardized hospital care, including physiotherapy, as needed. However, procedures for referrals to physiotherapy and staff resources are different in each center. At Copenhagen University Hospital, Rigshospitalet, children and adolescents are referred to physiotherapy when/if a physical deficit occurs (e.g., impaired gait and balance, drop feet, surgical operations). In contrast, at Aarhus and Odense University Hospital, all children are referred to physiotherapy at diagnosis. At all three centers, physiotherapy resources will be distributed according to the severity of illness and physical deficits.

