### Randomization

Following baseline assessment, participants will randomly be assigned to either the intervention group (integrative neuromuscular training + motivational-counseling sessions + usual care) or active control group (home-based training program + motivational-counseling sessions + usual care) by a blinded statistician using a computer-generated concealed allocation procedure to secure a proportionate stratified random sample with a (2:2) allocation. Participants will be stratified by sex, pubertal stage, and diagnosis as treatment for (1) solid tumors, (2) CNS-tumors, and (3) treatment for hematologic malignancy.

Baseline assessors and the statistician will be blinded to the allocation of participants; however, due to the nature of the intervention, neither participants nor intervention staff will be blinded throughout the intervention.

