### Statistical Considerations

Constrained longitudinal data analysis is applied to evaluate the intervention effectiveness by using constrained (generalized) linear mixed models in two scenarios. In the first one, predictors will include follow-up time points categorized as 3 and 6 months to account for any non-linear effect and dummy variables representing the intervention group at 3- and 6-month follow-ups, respectively. In the second scenario, the time variable will be treated as a continuous variable and an interaction between treatments (binary-coded, 1 representing intervention group), and the time variable will be included instead. Normal distribution will be applied on continuous outcome muscle strength, while binomial distribution will be applied on binary outcome metabolic syndrome. Baseline characteristics, such as age (as a continuous variable), gender, and type of cancer (categorized as solid, CNS, and hematologic tumors), will be included additionally as covariates in both scenarios. Patient identity will serve as a random intercept. Likelihood ratio tests based on maximal likelihood will be applied for the model selection of the fixed effects to determine linear or non-linear associations. Benjamin-Hochberg procedure will be applied to reduce the false discovery rate due to multiple comparisons. The level of significance is 0.05.

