### Design

We have chosen a randomized controlled design to provide evidence of the potential effectiveness of integrative neuromuscular training in children and adolescents during cancer treatment. This will allow us to minimize confounding factors, such as geographical differences in patient uptake and usual care at each center, which was considered a limitation to the previous RESPECT study (18).

This study includes all malignant diagnoses of pediatric cancer. Due to different treatment protocols, length of hospitalization, and the potential dysfunctions and side effects from the cancer disease itself, this creates heterogeneity within and between groups. We choose to include all diagnoses, firstly to secure sufficient power in the study population within a reasonable timeframe, thereby minimizing bias due to changes and development of treatment protocols. Secondly, and most importantly, by including all cancer diagnoses, which we have shown are both motivated and trainable (13, 18), we will increase the generalizability and external validity of this study. To minimize heterogeneity, the groups will be stratified by sex, pubertal stage, and diagnosis.

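### The covariates named for the mixed model leave out pubertal stage, which is a randomisation stratum, and centre; naming both is a minor, nearly free gain in precision

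*Protocol article*

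**What the plan says.** All of this is in the protocol article.

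- **Randomization:** "Participants will be stratified by sex, pubertal stage, and diagnosis", with diagnosis in three classes. The Design section repeats the three factors. Centre is not among them.
- **Statistical Considerations, model:** "Constrained longitudinal data analysis is applied to evaluate the intervention effectiveness by using constrained (generalized) linear mixed models in two scenarios". The baseline measurement of strength is therefore part of the model.
- **Statistical Considerations, covariates:** "Baseline characteristics, such as age (as a continuous variable), gender, and type of cancer", the last in three classes, and this applies to both scenarios. The only random effect given is for the patient: "Patient identity will serve as a random intercept". Neither pubertal stage nor centre is named.
- **Usual Care:** "procedures for referrals to physiotherapy and staff resources are different in each center". One hospital refers a child to physiotherapy when a deficit appears; the other two refer every child at diagnosis.

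**The concern.** A stratified randomisation removes part of the chance variation between arms in the stratifying factors. The analysis gets the credit for this only if it conditions on those factors. If a prognostic stratum is left out, the model still counts variation that the design has removed, and the standard error comes out somewhat too large. Age is a partial stand-in for pubertal stage, but the trial chose stage as a stratum in its own right.

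Centre raises a related question. Physiotherapy could affect leg strength, and its routine use differs by hospital. Since centre is not a stratum, the arms can differ by chance in their mix of hospitals, and the model as described has no term to take up that difference. What is at stake is precision, in a trial whose 106 evaluable children give just 80% power.

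**Working it through.** **Side by side**

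- Sex: stratum yes, named covariate yes.
- Diagnosis (three classes): stratum yes, named covariate yes.
- Pubertal stage: stratum yes, named covariate no.
- Age: stratum no, named covariate yes.
- Centre: stratum no, named covariate no.

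**The plan's own figure.** From the Sample Size section: mean 41.4 kg, difference 10% = 4.14 kg, spread 7.6, alpha 0.05 (taken as two-sided), power 80%. Then n per arm = 2 × (1.960 + 0.842)² × 7.6² / 4.14² = 52.9, rounded up to 53, or 106 in total. This matches the article. It uses 7.6 as a standard deviation although it is labelled SEM. That is a separate matter, but the kg figures below depend on it.

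**Pubertal stage, single follow-up.** Assumptions: 106 children, two pubertal levels tied to age, randomisation stratified by stage, age in the model, residual SD 7.6, 8,000 runs per setting. Baseline strength was not used.

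- Assumed pubertal effect 3 kg: mean SE 1.485 without stage and 1.480 with it, 0.3% lower.
- Assumed effect 6 kg: 1.514 and 1.480, about 2% lower.
- Type I error was 4.7–5.3% throughout, with or without stage.

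**Both factors, in the type of model the article describes.** Assumptions: 106 children, three visits, random intercept, age included, SD 7.6, within-patient correlation 0.5 unless stated, 1,500 runs per setting. The figures are the mean SE of the 6-month contrast, without and then with pubertal stage and centre.

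- Pubertal effect 3 kg: 1.276 and 1.275 (0.1%). At 6 kg: 1.285 and 1.276 (0.7%).
- Constant centre gap of 4 kg: 1.289 and 1.278 (0.9%).
- Centre gap growing to 4 kg by month 6, with by-visit terms: 1.298 and 1.284 (1.1%); at correlation 0.7, 1.082 and 1.060 (2.0%).
- Type I error without the covariates was 4.9–5.9%. With 1,500 runs its simulation error is √(0.05 × 0.95 / 1,500) = 0.56 points, so 5.9% is 0.9/0.56 = 1.6 such errors above 5%.

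**Centre-by-visit.** A further run (correlation 0.7, half the children from one centre, gap 0, 2 and 4 kg at the three visits, variance components taken as known) gave the actual spread of the 6-month estimate. It was 1.140 without centre, 1.124 with a centre main effect (1.4% lower) and 1.087 with centre by visit (4.6% lower). With a constant 4 kg gap nothing was gained. The 4.6% is larger than the 2.0% above because it is the spread of estimates across simulated trials, while the 2.0% is an average of model standard errors, whose residual variance is pooled over visits.

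**Chance imbalance of centre.** With an assumed share p = 0.5 from one hospital, the SD of the between-arm difference in that share is √(4 × 0.5 × 0.5 / 106) = 0.097. Its mean is zero.

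**The case against.** The covariate list opens as an illustration and is not closed. The article is condensed, it points to a fuller protocol on the registry, and an analysis plan may exist. So it is fair to say that the article does not name pubertal stage and centre, and too strong to say that it rules them out. The point survives because the article is not silent: it names covariates, gives their coding, applies them to both scenarios, and in doing so covers two of its three strata.

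It can also be objected that little is lost. Age, sex, diagnosis and baseline strength already carry most of what pubertal stage would add, and leaving out a stratum tends to make the inference conservative. This stands, and it is why the point is minor.

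A reader might infer that the Design section is wrong to say of randomisation: "This will allow us to minimize confounding factors, such as geographical differences in patient uptake and usual care at each center". It is not. The Choice of Comparators section explains that in the earlier study the passive comparators came from two centres, so centre and arm were confounded. Individual randomisation removes that. The statement does not promise adjustment for centre, and none is needed to make it true. The Explorative Outcomes section also plans to compare physiotherapy counts between groups and centres, so the co-intervention will at least be described.

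**Conclusion.** The mismatch is real and its effect is small. The treatment estimate is not biased, type I error stays close to 5%, and the sample size is unaffected. The cost is a standard error about 0–2% larger than necessary under the effects assumed above, plus chance imbalance of centre that the analysis could take out. The exception is a centre gap that is absent at baseline and reaches 4 kg by month 6. There a by-visit term cut the spread by nearly 5%, but such a gap is almost the size of the 4.14 kg target.

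Two stronger readings are tempting and unsupported.

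- A reader might infer a power gain of several points by shrinking the SD in the two-group formula by √(1 − R²). The documents give no R², and that formula does not describe a baseline-constrained mixed model in which age, sex, diagnosis and baseline strength are already used.
- A reader might infer that the primary estimate is shifted by some fraction of a kilogram through centre imbalance. Any such figure needs a centre gap and a centre share that the documents do not give, and the shift averages zero over repeated randomisations: it is sampling error and not bias.

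**What to change.** State in Statistical Considerations, or in the analysis plan before outcome data are examined by arm, that the primary and secondary models include age, sex, diagnosis, pubertal stage in the categories used for randomisation, and centre (three levels). Word this as a closed list, so that covariates cannot be added or dropped after the results are seen.

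A centre-by-visit term is optional. It helps only if differences between centres emerge after baseline. If it is wanted, it should be prespecified.

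Stage must be known in order to randomise, and centre is known for every child, so no new data are needed. The cost is a sentence of text and a few degrees of freedom. This is a free improvement of minor weight.

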### Trial Design

The INTERACT study is a national multicenter, two-arm parallel-group, randomized controlled superiority trial based on empirical evidence within the research group (13, 18, 43, 62) and methodical recommendations from current evidence (27). The primary endpoint is at 6 months after inclusion, and follow-up will be 12 months after ended treatment.

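### The primary strength model specifies only a patient random intercept, so the 6-month standard error is generally wrong, in either direction, if variance or correlation differs between visits

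*Protocol article*

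**What the plan says.** Statistical Considerations sets out the model: "Constrained longitudinal data analysis is applied to evaluate the intervention effectiveness by using constrained (generalized) linear mixed models in two scenarios". In the first scenario, "predictors will include follow-up time points categorized as 3 and 6 months to account for any non-linear effect", with treatment indicators at 3 and 6 months. The alternative is linear: "In the second scenario, the time variable will be treated as a continuous variable", with a treatment-by-time interaction. On the outcome distribution: "Normal distribution will be applied on continuous outcome muscle strength". On dependence between a child's repeated measurements there is one sentence: "Patient identity will serve as a random intercept". Age, gender and cancer type enter as covariates.

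The only model selection described concerns the mean: "Likelihood ratio tests based on maximal likelihood will be applied for the model selection of the fixed effects". No random slope, visit-specific variance, residual correlation structure or robust standard error is named. Trial Design places the primary comparison at the last of the three visits: "The primary endpoint is at 6 months after inclusion".

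**The concern.** With a normal outcome and independent residuals, a random intercept implies compound symmetry: the same variance at every visit and the same correlation for every pair of visits. In a constrained model the baseline measurement adjusts the 6-month contrast through that assumed covariance. The baseline–6-month correlation spans the longest interval, and the model replaces it with an average that includes the two shorter ones. If correlation fades with time, the model credits baseline with more predictive value than it has and the standard error is too small. If variance grows, the 6-month variance is averaged down, with the same result. If variance shrinks, the error runs the other way.

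The test of the sole primary outcome is at stake. The likelihood ratio tests compare fixed effects only, so nothing in the stated plan would detect or correct a wrong covariance. Choosing another covariance after seeing unblinded data would be data-driven.

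**Working it through.** **Inputs from the protocol article.** Mean 41.4, spread 7.6, 10% effect, alpha 0.05, power 80% and 106 children (Sample Size); visits at 0, 3 and 6 months and a patient random intercept (Statistical Considerations). **Assumed, because the article gives none:** correlations between visits, and SDs at 3 and 6 months relative to baseline.

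**The plan's own figure.** The effect is 0.10 × 41.4 = 4.14. With 7.6 used as an SD, n per arm = 2 × (1.960 + 0.842)² × 7.6² / 4.14² = 52.9, so 53 per arm and 106 in total. The figure reproduces. The calculations below therefore use 53 per arm and SD 7.6 at baseline.

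**Formulas (complete data, equal arms, categorical time).** Let s0, s3, s6 be the true SDs and c03, c36, c06 the true covariances. The random-intercept fit converges to

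- common variance v = (s0² + s3² + s6²)/3
- common covariance c = (c03 + c36 + c06)/3
- baseline adjustment slope b = c/v.

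The 6-month effect is the difference in 6-month means minus b times the difference in baseline means. Its variance is 2/53 times:

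- reported by the model: M = v(1 − b²)
- true: T = s6² − 2b·c06 + b²·s0².

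The SE ratio is q = √(M/T), and type I error = 2[1 − Φ(1.96q)]. With equal variances, T − M = 2b(b − c06/v). For positive correlations, the reported SE is then too small exactly when the average correlation exceeds the 0–6-month correlation.

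**Worked case, correlations 0.8/0.8/0.6 (0–3, 3–6, 0–6), constant SD.**

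- b = 2.2/3 = 0.733
- M = 1 − 0.538 = 0.462
- T = 1 − 2 × 0.733 × 0.6 + 0.538 = 0.658
- q = √(0.462/0.658) = 0.838; type I error = 2[1 − Φ(1.643)] = 10.0%
- In kg, the reported SE is 7.6 × √(0.462 × 2/53) = 1.00 and the true SE is 7.6 × √(0.658 × 2/53) = 1.20.

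**Other assumed patterns.**

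| Correlations 0–3/3–6/0–6 | SD relative to baseline | q | Type I error |
|---|---|---|---|
| 0.7/0.7/0.7 | 1/1/1 | 1.00 | 5.0% |
| 0.8/0.8/0.75 | 1/1/1 | 0.94 | 6.6% |
| 0.5/0.5/0.25 | 1/1/1 | 0.93 | 7.0% |
| 0.7/0.7/0.49 | 1/1/1 | 0.88 | 8.5% |
| 0.8/0.8/0.64 | 1/1/1 | 0.86 | 9.3% |
| 0.8/0.8/0.5 | 1/1/1 | 0.80 | 11.5% |
| 0.7/0.7/0.7 | 1/1.12/1.25 | 0.89 | 8.0% |
| 0.8/0.8/0.6 | 1/1.12/1.25 | 0.78 | 12.8% |
| 0.7/0.7/0.49 | 1/1.25/1.5 | 0.77 | 13.3% |
| 0.7/0.7/0.7 | 1/0.9/0.8 | 1.11 | 2.9% |
| 0.8/0.8/0.64 | 1/0.9/0.8 | 0.93 | 6.8% |
| 0.8/0.8/0.75 | 1/0.9/0.8 | 1.03 | 4.4% |

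**Checks.** Simulated REML fits (5,000 per scenario) gave 5.4% under true compound symmetry, 9.5–9.7% for 0.8/0.8/0.64, and 13.5–14.1% for 0.7/0.7/0.49 with SD 1/1.25/1.5. Each range covers 106 complete children and 127 with 20% dropout, so dropout changes little. The linear-time scenario behaves almost identically (9.3% for 0.8/0.8/0.64), so neither planned mean model avoids the problem.

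**With the covariance unrestricted.** A 6-month comparison using unrestricted visit variances and covariances (10,000 simulations, 106 complete children) had a type I error of 5.2–5.6% in four scenarios where the random-intercept model gives about 9–14%. When compound symmetry is true, a separate simulation gave power of 97.0% for a baseline-adjusted 6-month ANCOVA against 97.4% for the random-intercept model.

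**The case against.** **The direction is not documented.** This is the strongest point and it stands. A reader might infer that correlation will fall and spread will widen over six months of treatment in children aged 6 to 17.9, and that the type I error therefore about doubles. The article does not support that. It reports no correlations and no visit-specific SDs. Its remark on heterogeneity (Discussion, Design) concerns differences within and between groups, not variance rising over visits. Its Introduction describes lower-body strength as reduced early in treatment; if spread contracted along with the mean, the variance effect would reverse. Doubling needs a marked drop in correlation at moderate to strong levels, or substantial variance growth. Mild fading gives 6.6%, and mild fading with shrinking variance gives 4.4%.

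**The calculation omits the planned covariates.** Also true. The relevant correlations and SDs are those remaining after age, gender and cancer type, and adjustment will tend to lower the correlations. Weaker correlations reduce the inflation (7.0% for 0.5/0.5/0.25; 6.2% for 0.4/0.4/0.2) without removing it. The percentages illustrate sensitivity and are not estimates for this trial.

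**A separate analysis plan may settle the covariance.** This stands in part. The estimation method and degrees of freedom are details an article may leave out, and the text does not exclude extra residual structure or robust errors. But the article does not leave the dependence open: it names a structure, and as written that structure is compound symmetry.

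**Conclusion.** The point holds as a conditional one. As specified, the primary model imposes equal variances and equal correlations at three visits. Its 6-month standard error is in general wrong when those conditions fail, apart from chance cancellation of opposing departures. Under the assumed values, fading correlation and/or growing variance puts the type I error at about 6.5–14%, with about 10% for 0.8/0.8/0.6; the weakest correlations tried fall just below that range. Shrinking variance at constant correlation gives about 3%. Under true compound symmetry there is no error.

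The documents establish the restriction. They do not establish which departure will occur or how large it will be, so a claim that a positive result would be unreliable goes too far. The risk falls on the sole primary outcome and can be removed almost without cost, so the plan should be changed, but this is not a fatal flaw.

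**What to change.** Replace the random-intercept sentence, for the strength outcome, with an unstructured 3×3 within-child covariance over baseline, 3 and 6 months. Keep the constrained mean model, fit by REML with Kenward-Roger degrees of freedom, and test the 6-month treatment contrast from that fit. Name the random-intercept model with robust standard errors as the fallback if the unstructured model does not converge. Record this before unblinded outcome data are examined.

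The cost is one line in the analysis plan and four more covariance parameters (six instead of two), which about 106 children can support. The loss of power is negligible if compound symmetry is true: 97.0% against 97.4% in the simulated comparison, which used a 6-month ANCOVA as the analysis free of that assumption.

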**Methods:**

One hundred and twenty-seven children and adolescents, newly diagnosed with malignant and benign neoplasia, aged 6–17 years, and treated with chemotherapy or radiation will be randomized to either the intervention or the control arm of the study. The intervention group will, in addition to usual care, be offered a combination of 6 months of supervised physical exercise (integrative neuromuscular training) and home-based exercise. The active control group will, in addition to usual care, receive information along an unsupervised written home-based training program. All participants, including parents, will receive information about the importance of physical exercise during the course of cancer treatment, at the start of treatment, and in 5 monthly sessions. The primary outcome is measured in terms of isometric quadriceps muscle strength. Secondary outcomes include muscle strength and endurance, markers of metabolic syndrome and dysmetabolism, exercise capacity, physical function and activity, days of hospitalization, and health-related quality of life. Assessment will be conducted at treatment initiation (baseline), at 3 and 6 months after inclusion, and 1 month and 1 year after ended treatment. The primary endpoint for lower-body muscle strength is at 6 months after treatment initiation. The effects of the intervention will be evaluated through a constrained linear mixed model.

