## Introduction

In the Western world, the 5-year survival rate for children and adolescents diagnosed with cancer has improved progressively over the last 3 decades; from 72 in 1985 to above 85% in 2017 (1, 2). However, this improved rate is accompanied by an increase in both short- and long-term side effects (1, 2) and calls for novel strategies that work beyond sole survival as most children enter a negative loop where treatment-induced toxicities and a sedentary lifestyle exacerbate the physical deficits of cancer treatment (3–14).

Children and adolescents diagnosed with cancer are predominately treated with chemotherapy, radiotherapy, glucocorticoids, and surgery causing well-documented side effects, including damage to skeletal muscles, the central and peripheral nervous systems, and impaired cardiorespiratory fitness. This results in impaired gait (walking distance and reaction time) and balance, and it leads to fatigue and reduced physical activity (10, 15–18). Collectively, these factors have significant negative implications for physical health outcomes, including risk of muscle atrophy (10, 14, 19, 20), which persist into adulthood, as approximately two-thirds of cancer survivors have shown to have at least one chronic health condition 30 years after treatment initiation (8).

Skeletal muscles serve fundamental functions, ranging from generating mechanical force and mobility to regulating whole-body metabolic homeostasis (15). Hence, muscle atrophy and altered body composition with lower lean body mass and skeletal muscle index, seen after cancer treatment, threaten independent living due to reduced physical ability (15, 21–23). Muscle atrophy may also play an essential role in the development of dysmetabolism in long-term survivors, i.e., studies have reported increased prevalence of metabolic syndrome with physical inactivity being a predominant risk factor (OR, 1.7; 95% CI, 1.1–2.6) (24).

These severe physical and metabolic disturbances may be founded early during cancer treatment, as lower-body muscle strength and cardiorespiratory fitness are significantly decreased by 21 and 42%, respectively, within the first 30 days of treatment in children and adolescents compared to age- and sex-matched controls (10, 18), which highlights the need for early exercise interventions (13).

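### A likelihood ratio test on the outcome data chooses the primary model and test coefficient (6-month contrast or linear slope), although the endpoint is fixed at 6 months

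*Protocol article*

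**What the plan says.** The Abstract states: "The primary endpoint for lower-body muscle strength is at 6 months after treatment initiation". Trial Design agrees on the time point: "The primary endpoint is at 6 months after inclusion, and follow-up will be 12 months after ended treatment". The hypothesis at the end of the Introduction is also framed at 6 months.

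Statistical Considerations sets out two constrained longitudinal models. The first has categorical follow-up visits and "dummy variables representing the intervention group at 3- and 6-month follow-ups, respectively", so it contains a 6-month treatment coefficient. The alternative reads: "In the second scenario, the time variable will be treated as a continuous variable and an interaction between treatments" and time takes the place of those visit-specific terms. Both use the same random structure: "Patient identity will serve as a random intercept". The choice between them is then handed to the data: "Likelihood ratio tests based on maximal likelihood will be applied for the model selection of the fixed effects to determine linear or non-linear associations".

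The section does not say which coefficient gives the primary p-value. It also does not say that a 6-month contrast is reported whichever model is chosen.

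**The concern.** This is a stated rule, not a detail left for later. The endpoint is a difference at one visit, but the rule allows the reported treatment parameter to be a slope fitted through the 3- and 6-month visits together. Six times that slope equals the 6-month difference only if the effect grows in proportion to time. If the effect is reached early and held, or appears late, the slope model draws part of its 6-month value from the 3-month visit.

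Failing to reject linearity does not show linearity. At stake are a primary parameter known only after the data are seen, some bias under plausible effect shapes, and a p-value that takes no account of the selection step.

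**Working it through.** **Inputs from the protocol.** Mean 41.4 kg, spread 7.6 kg, 10% increase, alpha 0.05, power 80%, 106 children (Sample Size); equal allocation (Randomization); visits at 0, 3 and 6 months and a random intercept (Statistical Considerations).

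**Assumptions not in the protocol.** 7.6 is used as an SD (it is labelled a SEM, but only use as an SD gives 106); two-sided test; selection test at 5% on 2 degrees of freedom; within-child correlation ρ of 0.3, 0.5 or 0.8; flat control trend unless stated; no covariates and no dropout.

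**1. The protocol's own figure.** The difference is 0.10 × 41.4 = 4.14 kg. Per arm, n = 2 × (1.960 + 0.842)² × (7.6/4.14)² = 52.9, so 53, and 106 in total. This reproduces the stated number. It is a two-mean calculation, not one for a slope.

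**2. What each model estimates.** Let e3 and e6 be the true arm differences at 3 and 6 months. The categorical model targets e6. With an equal common correlation and k = ρ/(1 + 2ρ), the constrained linear model's 6-month value has expectation

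[0.5·e3 + e6 − 1.5k(e3 + e6)] / (1.25 − 2.25k).

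This equals e6 when e3 = e6/2. For ρ = 0.5, k = 0.25:
- plateau (4.14, 4.14): (6.21 − 3.105)/0.6875 = 4.52 kg, or +9%
- late (0, 4.14): (4.14 − 1.5525)/0.6875 = 3.76 kg, or −9%.

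The same formula gives ±13% at ρ = 0.3 and ±3% at ρ = 0.8. Simulated runs gave about 4–14% over the same range, which is the same within simulation error.

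**3. What the stated procedure estimates.** The line is used only when the test selects it. Simulated results for a true 4.14 kg at 6 months:

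| ρ | Line selected | Always-linear, plateau / late | Selected procedure, plateau / late |
|---|---|---|---|
| 0.3 | 58–59% | 4.69 / 3.59 | 4.35 / 3.92 |
| 0.5 | 44–46% | 4.52 / 3.76 | 4.26 / 4.04 |
| 0.8 | 8–9% | 4.28 / 4.00 | 4.15 / 4.12 |

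Averaged over selection, the error is therefore about 0–5%.

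**4. Power for a late 3 kg effect.** Selected procedure against fixed 6-month contrast: 0.52 against 0.56 at ρ = 0.3, 0.62 against 0.65 at 0.5, and 0.92 for both at 0.8.

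**5. Type I error.** Under the complete null (20,000 runs, ρ 0.3 to 0.7) the selected test rejects in 0.052–0.056 of trials and the fixed contrast in 0.053–0.054. With a transient 3-month effect of about 2–4 kg and none at 6 months, the selected test rejects in 0.046–0.079, the highest values being at ρ = 0.3. The fixed contrast stays at 0.046–0.060.

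**6. Dependence on the control trend.** One degree of freedom of the selection test responds to curvature in the shared time trend, the other to curvature in the treatment effect. A fall of 0.21 × 41.4 = 8.7 kg by 3 months, then held, leads to the line being selected in about 1% of trials or fewer. The selected and categorical estimates then coincide. A milder held fall of 2 kg with a plateau effect at ρ = 0.5 leads to the line being selected in about 70% of trials, with a selected estimate of about 4.3 kg.

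**The case against.** The strongest reply is that little goes wrong in practice, and much of it stands.

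- A reader might infer an inflated false-positive rate. The calculations do not support that: error is about 5% under the complete null and at most about 8% in the transient-effect settings run.
- A reader might take the error of the always-linear model (about 9% at ρ = 0.5), or its power of 58% against 66% for a late 3 kg effect, as the harm. Those figures describe a model the protocol would use only when it is selected. The procedure's own bias and power loss are smaller.
- A reader might cite the 21% strength deficit in the Introduction as proof that the course is not linear. That deficit is measured "within the first 30 days of treatment in children and adolescents compared to age- and sex-matched controls". It is not a change within child, and its window overlaps a baseline taken up to 14 days after treatment starts. A sustained fall of that size would also make the selection rule harmless, because the line would almost never be selected.
- A reader might say the endpoint itself is open. It is not: the time point is 6 months throughout, and a linear model still yields a 6-month value. What is open is the model and the coefficient tested.

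Finally, this is a condensed article, and an analysis plan not shown may settle the test threshold and the reported contrast. That is fair for the details. It does not answer the selection rule, which the article states outright and which an analysis plan following it would inherit.

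**Conclusion.** The point holds as a matter of pre-specification and interpretability. The primary model and test coefficient depend on the outcome data, while the endpoint and sample size both point to a 6-month difference.

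The size is modest. Under the flat-trend assumptions above, the selected procedure's 6-month estimate is off by about 0–5% on average for a plateau or late 4.14 kg effect. When the line is used throughout, the error is about 3–14%, and the line is selected in about 8–59% of trials. Power for a late 3 kg effect falls by 0–4 points. These figures rest on a correlation, a selection threshold and a control trend that the protocol does not give. They shrink towards zero at high correlation or with a strongly curved trend. No claim of material alpha inflation is made.

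**What to change.** In Statistical Considerations, name the 6-month treatment coefficient from the categorical-time constrained model as the single primary test. Remove the likelihood ratio selection for the primary outcome. Keep the continuous-time slope model as a labelled sensitivity analysis.

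This is a one-sentence change that needs no new data and no change to the sample size. If the effect is exactly linear, it costs about 1 point of power at ρ = 0.5 (0.90 against 0.91 for 4.14 kg) and about 2–3 points at ρ = 0.3.
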